### Outcome measurements

#### Primary outcome measure

##### Pulmonary function (FEV_1_)

Pulmonary function (FEV_1_) will be evaluated prior to treatment, at weeks 26 and 52 of the treatment phase, and weeks 26 and 52 of the follow-up phase.

##### Exacerbation

Frequency of exacerbations of COPD will be evaluated at weeks 26 and 52 of the treatment phase, and weeks 26 and 52 of the follow-up phase. If the interval between two onsets of acute exacerbation is within 5 days, it can be counted as one period of acute exacerbation.

#### Secondary outcome measure

##### Dyspnea

The Dyspnea Scale Questionnaire, which was first developed by the British Medical Research Council (MRC) and later revised by the American Thoracic Society (MMRC), will be observed and recorded prior to treatment at weeks 13, 26, 39 and 52 of the treatment phase, and weeks 26 and 52 of the follow-up phase.

##### Quality of life (QOL)

The secondary outcome measures will be QOL improvement assessed by using the COPD Assessment Test (CAT) [14] and short-form 36-item questionnaire (SF-36) [15]. They will be observed and recorded prior to treatment, at weeks 13, 26, 39 and 52 of the treatment phase, and weeks 26 and 52 of the follow-up phase.

##### The 6-Min walking distance test (6MWD)

In patients with COPD, the 6 MWD is a good predictor of health-care utilization. The 6MWD will be observed and recorded to prior treatment, at weeks 13, 26, 39 and 52 of the treatment phase, and weeks 26 and 52 of the follow-up phase.

#### Adverse event reporting

pirometry at each site will be conducted using SpiroUSB™ (CareFusion) and Spida5® software. Routine calibration and standard operating procedures will be uniformly undertaken at each site. Participants will be advised not to use respiratory medications for several hours prior to their spirometry testing. Two sets of measurements will be taken at each visit, pre-bronchodilator and post-bronchodilator (post 400 μg of inhaled salbutamol).

Any adverse events will be listed in the trial record and followed up to completion by the trial coordinators and respiratory physicians. Adverse event details will be scored using a six-point scale: 0 = none, 1 = minimal, 2 = mild, 3 = moderate, 4 = severe and 5 = extremely severe. Participants will be able to report adverse events anytime throughout the trial and will receive advice accordingly. Serious adverse events will be reported to the reviewing Human Research Ethics Committee (HREC) and site HRECs within the timeframe specified by the lead HREC.

Throughout the study period, trial coordinators will contact the participant’s usual treating doctor to record relevant data on presentations and exacerbations.

To assist with outcome documentation and medication compliance, participants will be given a participant diary for the duration of the trial. They will be asked to record trial medication and relief medication usage as well as any new medications they commence during the trial.

Participants may withdraw from the study for any reason at any time without repercussions. They will only be withdrawn by investigators if it is deemed medically unsafe for them to continue. Dropouts will not be replaced.

### Statistical analysis

Descriptive statistical analysis will be performed for all the study variables. We will calculate the mean, median and standard deviations for quantitative variables, and the absolute and relative frequency for qualitative variables.

We use SPSS 19.0 (license no.: 6f1d84c801f1e6010dc, SPSS Inc., Chicago, IL, USA) to statistically analyze the data. An intention-to-treat analysis will be applied using the Last Observation Carried Forward (LOCF) method. Analysis of covariance with baseline as covariate will be used to assess differences in treatment outcomes between the two groups at each of these time points. To correct for inflated risk of type 1 error, multiple comparison procedures suggested by Ludbrook et al. will be used [16]. The use of relief medication during the trial will be investigated for its effect on the outcome measures by using it as a covariate in the statistical analysis. A Data Safety Monitoring Board has been established to assess the progress of the trial, particularly safety endpoints.

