### Sample size

The sample size calculation is based on the annual decline of mean forced expiratory volume in 1 s (FEV_1_) in COPD subjects. The previous study showed that the mean rate of change in FEV_1_ was a decline of 51 ml per year in patients with TCM treatment and 131 ml per year in patients with usual care with mild/moderate COPD. According to the sample size of the estimation formula $n=2{\left[\frac{(u_{a}+u_{\varphi })\sigma }{\delta }\right]}^{2}$, n1 = n2 = 2(1.64 + 1.28)^2^ × 0.28^2^/0.08^2^ = 209. It is estimated that a sample size of 209 subjects per group will be required, considering 20% drop out and exit. This results in 504 in total. Intention-to-treat analysis will be applied to minimize bias due to drop-outs.

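### LOCF is the stated intention-to-treat method for FEV1, an outcome the article itself expects to fall every year, so the decline of patients who drop out is frozen

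*Protocol article*

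**What the plan says.** The Statistical analysis section fixes how missing data are handled: "An intention-to-treat analysis will be applied using the Last Observation Carried Forward (LOCF) method". It then fixes the model, to be applied visit by visit: "Analysis of covariance with baseline as covariate will be used to assess differences in treatment outcomes between the two groups at each of these time" (final word of the sentence omitted). No other missing-data method is named.

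FEV1 is a primary outcome. It is measured before treatment and then "at weeks 26 and 52 of the treatment phase, and weeks 26 and 52 of the follow-up phase". The second year is off treatment (Study design).

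The Sample size section is built on FEV1 decline. Its source is a previous study in which "the mean rate of change in FEV_1_ was a decline of 51 ml per year in patients with TCM treatment". For the comparison group the figure was "131 ml per year in patients with usual care with mild/moderate COPD". The total is set "considering 20% drop out and exit". The same section gives the purpose of intention-to-treat: "Intention-to-treat analysis will be applied to minimize bias due to drop-outs". The section headed Adverse event reporting adds that patients who drop out are not replaced.

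**The concern.** Carrying a value forward assumes that FEV1 stays flat from the last visit onward. The Sample size section assumes the opposite in both arms, and the difference between the two slopes is the treatment effect the trial is designed to detect. FEV1 is measured only every 26 weeks. A patient lost after the week 26 visit therefore has half of the year's decline removed. One lost before that visit has all of it removed, if baseline is carried.

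Two consequences follow. If the treatment works as planned and loss is equal, the observed difference is too small, because more decline is erased in the arm that declines faster. If loss is unequal, the arm that loses more patients looks better preserved for that reason alone.

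The follow-up year has a further problem. For a patient lost during treatment, LOCF reports a baseline or on-treatment value as an off-treatment result at weeks 26 and 52 of follow-up, that is, 78 and 104 weeks after the start.

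**Working it through.** **Inputs from the article**
- Decline on TCM 51 ml/year; on usual care 131 ml/year; difference 131 − 51 = 80 ml (Sample size).
- SD 0.28 L, difference 0.08 L, drop-out 20% (Sample size).
- FEV1 at baseline and every 26 weeks (Primary outcome measure).

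**The plan's own figure.** The article gives "n1 = n2 = 2(1.64 + 1.28)^2^ × 0.28^2^/0.08^2^ = 209". Check: 2 × 2.92² × 0.0784 / 0.0064 = 2 × 8.5264 × 12.25 = 208.9, which rounds to 209. This reproduces, and it confirms that an 80 ml difference in yearly decline is the design target.

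**Assumptions added here**
- Decline is linear within the year.
- Drop-outs would have kept their arm's mean slope.
- The usual-care slope applies to the placebo arm.
- Where a patient has no post-baseline FEV1, baseline is carried. The article does not say whether it is.

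**Formula.** Let D be an arm's yearly decline, c its share of drop-outs, and f the fraction of the year elapsed at the carried value (0 = baseline, 0.5 = week 26). The expected week-52 decline under LOCF is

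D × [(1 − c) + c × f].

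The expected difference is therefore

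80 − (1 − f) × (131 × c_control − 51 × c_TCM).

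Baseline adjustment does not remove this, because the missing decline occurs after baseline.

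**Equal 20% loss, planned effect true**
- All lost after week 26 (f = 0.5): control 131 × 0.9 = 117.9; TCM 51 × 0.9 = 45.9; difference 72.0 ml, a bias of −8 ml (−10%).
- All lost before week 26 (f = 0): control 131 × 0.8 = 104.8; TCM 51 × 0.8 = 40.8; difference 64.0 ml, a bias of −16 ml (−20%).

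**Unequal loss, planned effect true** (assumed splits averaging the stated 20%)
- TCM 10%, control 30%: 62.9 ml (f = 0.5) or 45.8 ml (f = 0).
- TCM 30%, control 10%: 81.1 ml or 82.2 ml.
- The bias is zero only when TCM loss is 131/51 = 2.57 times control loss.

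**No true effect, both arms falling 131 ml/year.** The false difference is 131 × (1 − f) × (difference in loss).

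| Loss (assumed unless 20% v 20%) | Week 26 carried | Baseline carried |
|---|---|---|
| 20% v 20% | 0 ml | 0 ml |
| 25% v 15% | 131 × 0.5 × 0.10 = 6.6 ml | 131 × 0.10 = 13.1 ml |
| 30% v 10% | 131 × 0.5 × 0.20 = 13.1 ml | 131 × 0.20 = 26.2 ml |

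The false difference always favours the arm with more losses. The article gives no slope for the off-treatment year, so the effect on the follow-up visits is not sized here.

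**The case against.** The main points on the other side are these.

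- **Under the stated inputs the harm is modest and conservative.** The article gives one drop-out figure, 20%, and describes a blinded placebo-controlled trial. With equal loss, LOCF attenuates a true effect by 8 to 16 ml, and with no effect it is unbiased. This stands. The false differences rest on assumed splits and show what could happen, not what the article predicts.
- **Power.** A reader might infer that LOCF cuts two-sided 5% power from 89% to 82% or 73%. That does not hold. The 89% is for 252 per arm with no drop-out. An unbiased analysis of about 202 completers per arm (252 × 0.8) has about 82%. The 73% keeps the SD at 280 ml although a fifth of the changes would be exactly zero. Taking 280 ml as the SD of change, the variance in each arm is 0.8 × 280² + 0.16 × D². The standard error is then √[(65,466 + 63,136)/252] = 22.6 ml, and power is about 81%. The 1.64 in the article's formula is also not a two-sided 5% value.
- **Type I error.** A reader might go on to quote an inflated error rate. The documents give no unequal split, and the rate depends on the split, the variance and the sidedness assumed. None is quoted here.
- **The purpose sentence.** The Sample size section credits intention-to-treat, not LOCF, with reducing drop-out bias. The article does not claim that LOCF itself does so.
- **Other outcomes.** A reader might extend the argument to MMRC, CAT, SF-36 and 6MWD. A yearly decline is stated only for FEV1, so the argument does not reach them.
- **Detail left to an analysis plan.** This does not answer the point, because the article itself names the method.

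**Conclusion.** The concern holds for FEV1. The article prescribes a method that assumes no further decline, for an outcome it expects to decline in both arms. Under its own slopes and an equal 20% loss, the expected week-52 difference is 64 to 72 ml instead of 80 ml. The 64 ml end requires that baseline be carried.

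The direction is not fixed in general. With no true effect and equal loss and timing there is no bias. With unequal loss the arm losing more patients gains a false advantage: about 7 to 13 ml at an assumed 25% v 15%, and 13 to 26 ml at an assumed 30% v 10%, if both arms fall 131 ml/year. All these sizes rest on linear decline and on drop-outs keeping their arm's mean slope. The finding is one of bias; it does not establish a power loss or a particular false-positive rate.

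**What to change.** Make the primary FEV1 analysis a mixed model for repeated measures on all observed visits, adjusted for baseline, with the treatment contrast estimated at week 52 of treatment and no values carried forward. State that it is valid under missing at random. Add one sensitivity analysis under missing not at random, for example delta-adjusted or placebo-based multiple imputation. Keep LOCF at most as a sensitivity analysis, and if it is kept, say whether baseline is carried for patients without a post-baseline FEV1.

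The cost is a change of analysis wording and modest extra programming; no new data are needed. The downside is reliance on the missing-at-random assumption, which the sensitivity analysis is there to test. The Trial status section reports 150 of 504 patients recruited at submission, so as of that date the change could be made before unblinding.

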**Methods and design:**

A prospective, multi-center, double-blinded and randomized controlled method will be used to test the therapeutic effects of TCM treatment according to syndrome differentiation. A total of 504 patients will be enrolled into this study with 252 in each treatment group. Patients will receive medication according to their assigned group. TCM for COPD will be administered twice daily over 52 weeks, and all patients will follow the treatment program for 52 weeks. The FEV_1_ and exacerbations will be used as the primary outcome measures. The quality of life and the Modified Medical Research Council (MMRC) Dyspnea Scale, and the 6-min walk test (6MWD) will be used as the secondary outcome measures.

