### Objective

To determine whether treatment with TCM with syndrome differentiation reduces exacerbation frequency.

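### Baseline-adjusted ANCOVA with LOCF, set for all outcomes, does not fit exacerbation frequency: no pre-treatment count is listed and time at risk is ignored

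*Protocol article*

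**What the plan says.** The Objective section has one aim: "To determine whether treatment with TCM with syndrome differentiation reduces exacerbation frequency". The abstract's methods paragraph pairs FEV1 with this outcome: "exacerbations will be used as the primary outcome measures".

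The Exacerbation section sets the schedule: "Frequency of exacerbations of COPD will be evaluated at weeks 26 and 52 of the treatment phase". Its schedule for the follow-up year uses the same two weeks. It lists nothing before treatment. It also defines how episodes are merged: "If the interval between two onsets of acute exacerbation is within 5 days, it can be counted as one period of acute exacerbation". The outcome is therefore a count of recurrent events. FEV1, by contrast, "will be evaluated prior to treatment, at weeks 26 and 52 of the treatment phase" and again in follow-up.

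The Statistical analysis section gives one between-group method, at each time point and with no outcome exempted: "Analysis of covariance with baseline as covariate will be used to assess differences in treatment outcomes between the two groups". For missing data it says: "An intention-to-treat analysis will be applied using the Last Observation Carried Forward (LOCF) method". The Sample size section expects 20% drop-out, and the Adverse event reporting section says that drop-outs are not replaced.

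**The concern.** Two parts of the prescribed method do not match this outcome. The covariate that the model calls for is absent from the exacerbation schedule. LOCF, which is meant for a measurement repeated at visits, is applied to a count that grows with time under observation.

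At stake is the result for the trial's stated objective. If the carried value is a count over less than a year, a patient who leaves early contributes fewer events only because fewer could be seen. Should the arms differ in drop-out, that shortfall enters the treatment comparison and can create or hide an apparent benefit. Patients who leave before the first scheduled count may also fall out of an analysis that is described as intention-to-treat.

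**Working it through.** **The plan's own figure.** The only calculation in the article is for FEV1: 2 × (1.64 + 1.28)² × 0.28² / 0.08² = 208.9, so the stated 209 per group reproduces. It does not bear on exacerbations, for which no rate or sample size is given. The inputs used here are the 20% drop-out and the 252 patients per arm.

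**Schedules side by side.** FEV1, dyspnea, CAT/SF-36 and 6MWD each list an assessment before treatment. Exacerbations list weeks 26 and 52 of treatment and of follow-up only. Exacerbation history is not an eligibility criterion or a stratification factor. On the stated schedule there is no baseline value for the covariate, and no value to carry forward before week 26.

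**Three readings of LOCF for the year's count.** The article does not say whether the count is cumulative or per interval. Let d be the proportion dropping out. Assume that drop-out times are uniform over the 52 weeks and unrelated to outcome. The mean analysed count, as a fraction of the true yearly rate, is then:

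- A, cumulative count frozen on the day of leaving: (1 − d) + 0.5d = 1 − d/2. This is 0.90 at d = 0.2, 0.95 at 0.1 and 0.85 at 0.3.
- B, cumulative count carried from the last scheduled visit, with those leaving before week 26 excluded: [(1 − d) + (d/2)(0.5)] / (1 − d/2). This is 0.944 at d = 0.2, 0.974 at 0.1 and 0.912 at 0.3.
- C, 26-week interval count repeated, with the same exclusion: [(1 − d) + d/2] / (1 − d/2) = 1 for every d.

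With equal 20% drop-out the yearly count is thus understated by 10% under A, about 6% under B and not at all under C. With 10% versus 30% drop-out and no true effect, the false difference is (0.95 − 0.85) × rate under A and (0.974 − 0.912) × rate under B. For assumed rates of 0.5, 1.0 and 1.5 per year that is 0.05, 0.10 and 0.15 exacerbations per patient under A, and 0.03, 0.06 and 0.09 under B. Under B and C a share d/2 has no scheduled value: 0.10 × 504, or about 50 patients, at 20% drop-out.

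**Effect on the test.** This was simulated with 252 per arm, gamma-Poisson counts with assumed dispersion 0.7, and a two-sided nominal 5% level. The LOCF analyses compare mean counts without a covariate, since none is listed. The rate model is a log rate ratio with time at risk and robust variance.

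| Setting | A | B | C | Rate model |
|---|---|---|---|---|
| No effect, 20% in both arms | 4–6% | about 5% | about 5% | about 5–6% |
| No effect, 10% vs 30% | 11–17% | 7–9% | 5–6% | about 5% |
| Power, rate ratio 0.7, rate 1.0, equal drop-out | 78% | – | about 75% | about 80% |
| Power, 30% control vs 10% TCM | 47% | – | 75–76% | about 80% |
| Power, 10% control vs 30% TCM | 95–96% | – | 75–76% | about 80% |

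Ranges run over the three assumed rates. The simulation error at 17% with 1,500 runs is √(0.17 × 0.83 / 1500), about 1 percentage point. With a milder 15% versus 25% split, reading A gives 6 to 8%.

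**The case against.** The strongest reply is that the harm is conditional. It needs a particular reading of LOCF and unequal drop-out, and the article gives only 20% overall. Nothing in it points to a threefold imbalance between blinded arms. Under the interval reading, which the wording about each time point allows, the bias disappears. With equal drop-out every reading keeps its type I error. All of this stands and limits the size of the point.

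It is also fair that the methods section never names exacerbations, that an endpoint-specific model is often left to the analysis plan, and that a comparison of mean counts performs acceptably at this sample size: 78% power against about 80%. Skewness alone is therefore no strong argument. But the article is not silent here. It states one rule for all outcomes, and an analysis plan would have to depart from that rule to suit this one.

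Three stronger readings are tempting and are not supported:

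- That the analysis cannot be run. Without a baseline value, ANCOVA reduces to a comparison of means, which can be run.
- That no baseline count is collected. The article lists none, but it condenses a fuller protocol, and the Exclusion criteria section mentions further baseline testing without detail.
- That the arm with more drop-out always looks better. This is true when a cumulative count is carried, not when interval counts are repeated.

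**Conclusion.** The point holds as a mismatch between a stated method and the outcome that carries the trial's objective. The prescribed covariate is not on the exacerbation schedule, and LOCF on a count does not account for time at risk.

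Its size is conditional. If cumulative counts are carried, the yearly count is understated by about 6 to 10% at 20% drop-out. If drop-out also differs between arms as assumed, type I error is about 7 to 17% and power moves in either direction. If interval counts are repeated, or drop-out is equal, type I error holds. With interval counts what remains is a small loss of efficiency (about 75% against 80% power) and the patients who leave before week 26 with nothing to carry.

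The exacerbation rates, dispersion, drop-out split and uniform drop-out times are assumptions, not figures from the article. All results also assume that drop-out is unrelated to outcome. A reader might infer that a false positive is likely, but the article gives no evidence of unequal drop-out to support that.

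**What to change.** - Restrict baseline-adjusted ANCOVA to the continuous outcomes.
- Analyse the number of exacerbations over the 52-week treatment phase by negative binomial regression, or Poisson regression with robust variance. Use log time under observation as the offset and arm, syndrome and site as factors; syndrome and site match the stratification and the site-specific lists.
- Include every randomised patient with any observation time, impute no counts, and report the rate ratio with its 95% confidence interval.

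The cost is analysis wording only, best settled before unblinding. The Adverse event reporting section already has coordinators obtain exacerbation data from treating doctors throughout the study, and the 5-day rule implies that onset dates are known. The participant diary should not be relied on for this, because it is described for medication use.

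A prior-year exacerbation count as covariate is not worth adding unless it can also be obtained for the 150 patients already recruited at submission. Otherwise it would be missing for 150/504, about 30%.

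### The Objective, the two primary outcomes, the corrected tests and the sample size do not match, so the implied 90% power does not apply to the tests the plan describes

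*Protocol article*

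**What the plan says.** Five places in the Protocol article bear on this.

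- **Objective.** There is one objective: "To determine whether treatment with TCM with syndrome differentiation reduces exacerbation frequency".
- **Abstract and Primary outcome measure.** "The FEV_1_ and exacerbations will be used as the primary outcome measures". Nothing says whether one ranks above the other, or whether success on either or on both is required. FEV1 and exacerbations are each evaluated at weeks 26 and 52 of treatment and again at weeks 26 and 52 of follow-up. Under Study design, follow-up is a separate 52-week phase after the 52 weeks of treatment.
- **Statistical analysis.** Analysis of covariance, adjusted for baseline, is to assess differences "between the two groups at each of these time points. To correct for inflated risk of type 1 error, multiple comparison procedures" from a cited paper are to be used. No principal outcome or visit is named.
- **Sample size.** "The sample size calculation is based on the annual decline of mean forced expiratory volume in 1 s", and the calculation is "n1 = n2 = 2(1.64 + 1.28)^2^ × 0.28^2^/0.08^2^ = 209". With 20% allowed for loss, the total is 504. No exacerbation rate or effect appears.
- **Adverse event reporting (spirometry paragraph).** "Two sets of measurements will be taken at each visit, pre-bronchodilator and post-bronchodilator". The article does not say which set supplies the primary FEV1.

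**The concern.** The question asked, the outcomes called primary, the tests to be run and the calculation that justifies 504 patients should describe one trial. Here they differ. The stated objective has no part in the sample size, and the outcome that sets the sample size is absent from the Objective. The analysis corrects for multiple testing, but the sample size leaves no room for that correction.

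Two things are at stake. The first is power: a correction spread over several visits, half of them after treatment ends, takes power from the one-year FEV1 comparison for which the trial was sized. The second is interpretation: the article does not let a reader say beforehand which result would make the trial positive.

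**Working it through.** **Inputs (Sample size section).** The difference is 131 − 51 = 80 ml per year, or 0.08 L. The standard deviation is 0.28 L. The multipliers are 1.64 and 1.28. Alpha, sidedness and power are not given in words; 1.64 corresponds to one-sided 5% (equivalently two-sided 10%) and 1.28 to 90% power.

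**Reproducing the plan's figure.** n = 2 × (1.64 + 1.28)² × 0.28² / 0.08² = 208.9, so 209 per group. With unrounded normal quantiles it is 210, and 210 × 1.2 = 252 per arm, or 504 in total. A two-sided 5% test would need 258 per arm. The stated figure is therefore one FEV1 comparison at one-sided 5% with no multiplicity adjustment.

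**Counting the tests.** Two primary outcomes at four post-baseline visits give 2 × 4 = 8 comparisons. This takes the time points in the analysis section to be the visits listed under the primary outcomes. A family of 4 would arise from, for example, both outcomes at the two treatment-phase visits. A family of 2 is both outcomes at one visit.

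**Power after correction.** The article does not name the procedure, so Bonferroni is assumed. For m tests,

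power = Φ( 0.08 / (0.28 × √(2/n)) − z ),

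with z the upper 0.05/m point (one-sided) or the upper 0.05/(2m) point (two-sided). The first term is 2.92 at n = 209 and 3.21 at n = 252. For example, with n = 209, one-sided and m = 8, z = 2.50 and Φ(2.92 − 2.50) = 66.4%.

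| Tests m | One-sided 5%, n = 209 | One-sided 5%, n = 252 | Two-sided 5%, n = 209 | Two-sided 5%, n = 252 |
|---|---|---|---|---|
| 1 | 89.9% | 94.1% | 83.2% | 89.4% |
| 2 | 83.2% | 89.4% | 75.2% | 83.3% |
| 4 | 75.2% | 83.3% | 66.4% | 76.1% |
| 8 | 66.4% | 76.1% | 57.4% | 68.2% |

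The 209 columns use the calculated requirement. The 252 columns use everyone randomized, which is nearer to the planned intention-to-treat set with last observation carried forward, and they assume that carrying values forward does not dilute the effect.

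**Exacerbations.** The documents give no event rate, dispersion or effect, so no power can be derived.

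**The case against.** The strongest reply is that a journal article may leave the multiplicity procedure to an analysis plan that is not shown here. The correction itself is planned, so type I error is not left unprotected. Bonferroni over eight tests is close to the worst case, and Holm relaxes its threshold once other tests reject. If success required both outcomes, no alpha would need to be split between them. Baseline adjustment could shrink the residual standard deviation. And because the trial is sized on annual decline, one year is the natural time for FEV1.

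Much of this stands. The missing name of the procedure is no fault, and the size of the loss is conditional. But the mismatch does not depend on the missing detail: objective, primary outcomes and sample size are protocol-level statements, and they disagree in this document. A both-required rule is not stated, and it would leave the correction across visits in place. The article claims no gain from baseline adjustment and gives no correlation from which to compute one. The one-year basis of the sample size is not carried into the analysis section, which treats all visits alike.

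Some stronger readings are tempting but unsupported:

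- *Twelve primary tests.* Counting pre- and post-bronchodilator FEV1 separately gives 4 + 2 × 4 = 12, but the spirometry paragraph describes measurement and does not say that both are tested as primary.
- *A familywise error of about 34%* (1 − 0.95⁸, for independent tests). This describes uncorrected testing, and the plan corrects.
- *Week 26 as an interim look.* It is a repeated assessment; the article describes no interim efficacy analysis.

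**Conclusion.** The point holds as a mismatch. The 90% power implied at 209 per group belongs to one unadjusted, one-sided FEV1 comparison and does not hold for FEV1 tests under the planned correction. On the plan's own one-sided level, with Bonferroni assumed, power at 209 per arm falls to between 83% (two tests) and 66% (eight tests).

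A reader might take the 57% for eight two-sided tests at 209 per arm as the size of the problem. That figure combines a near-worst-case correction with a change from the plan's one-sided level, and sidedness is a separate matter. Nor can a detectable exacerbation effect be attributed to this plan: any such figure would rest on rates the documents do not give.

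The results assume the protocol's difference and standard deviation, no gain from baseline adjustment, and that the tested visits are those listed under the primary outcomes.

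**What to change.** 1. Name week 52 of the treatment phase as the primary time point: FEV1 at week 52, and the exacerbation rate over weeks 0 to 52.
2. Control the error rate across these two comparisons only, by Holm or by a fixed sequence with the order stated. Make week 26 and all follow-up-phase comparisons secondary.
3. State whether pre- or post-bronchodilator FEV1 is primary.
4. Amend the Objective to list both primary outcomes.
5. Restate FEV1 power at the adjusted alpha, with its sidedness. Give the exacerbation rate ratio detectable at that alpha, under stated assumptions on rate and dispersion.

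This does not restore 90% in every case. At Holm's first step (alpha/2), FEV1 power is 83% one-sided or 75% two-sided at 209 per arm (89% or 83% at 252). In a fixed sequence with FEV1 first, FEV1 keeps the single-test power; if it comes second, its power also depends on the exacerbation result. Either way, power is no longer lost to the other visits, and the stated figure matches the test.

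The cost is wording and a protocol amendment during recruitment (150 patients had been recruited at manuscript submission). Week 26 and follow-up results lose confirmatory status. No extra patients, visits or measurements are needed.
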